#### Development of data collection tools and their validation

The data collection tools will be developed by public health experts based on a review of available literature, standard treatment guidelines for snakebite, and consultation with the TAC.

*Retrospective and Prospective data form*. These two data collection forms will include questions about the basic demographic characteristics of the snakebite victim followed by details of the event of snakebite, signs and symptoms, first aid, and steps taken for the management including usage of anti-venom. The forms will have a separate ‘Follow Up’ section for transferred out patients. Hospital records will be used for form filling.

*Facility Survey Questionnaires*. Separate questionnaires will be developed for Primary Health Centre (PHC), Rural Hospital (RH) / Community Health Centers (CHC), and Sub District Hospital (SDH) / District Hospital (DH) to document staff positions, drugs, equipment, anti-venom availability and utilization, infrastructure, laboratory investigations, and Information Education Communication (IEC) materials and activities. The questionnaires will concur with the Indian Public Health Standards (IPHS) Guidelines and STG, 2017 for respective facilities.

*Focused Group Discussion (FGD) Guide*. The FGD guide will consist of open-ended, semi-structured questions to elicit the knowledge, awareness, and perceptions of people in the study area regarding snakes and snakebites, first aid, prevention methods, management, and health-seeking behavior. The FGD guide will be developed in English and later translated to local languages.

*Questionnaire for healthcare providers*. Separate questionnaires for peripheral workers and Medical Officers (MO) at facilities would be developed based on the STG, 2017 and WHO SEARO Guidelines for management of snakebites. They will try to capture the knowledge, perceptions, and experiences of healthcare providers regarding snakes and snake bites, anti-venom use, challenges encountered while managing snakebite cases at public health facilities.

All the developed tools will be validated through the following methods–

*Face Validity*. The TAC will critically review the tools to confirm that they have sufficient and pertinent information to gather the knowledge, awareness, and perceptions of the respondents. The panel will be asked to comment on the relevance, language, ease of understanding, and ability of the questions to elicit desired responses.

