#### Phase I–Retrospective data collection, facility surveys, and FGDs in the community

Two-year retrospective data (01 January 2020 to 31 December 2021) will be collected from all the public health facilities in study areas where snakebite management is expected to be provided. This includes all the Primary Health Centers, Rural Hospitals / Community Health Centers, Sub District Hospitals and District Hospitals. Medical Colleges where severe cases are referred from the study blocks will also be included to ensure quality retrospective data collection. Additional data on snakebite deaths will also be collected from local authorities, panchayat office, registrar of births and deaths so that maximum deaths are captured. A cross-sectional survey will assess the preparedness of the public health facilities for SBE management. Retrospective data and facility data will be collected and entered into an online application. The captured data will be verified at regular intervals by the study coordinator.

The qualitative component will involve conducting community FGDs in the study areas. Total 24 FGDs will be conducted, six per block (three male, three female). Each FGD will be restricted to 8 to 16 participants. Actual number of FGDs may vary according to the saturation of responses. FGDs will be conducted at common and acceptable community places. The Primary Health Centers (PHCs) in the block would be enlisted and one random village would be picked per PHC. The information about conduct of a FGD would be given to the villagers with the help of the frontline community healthcare workers and community leaders and 8–16 randomly selected participants would be invited to participate. Participants belonging to the community and above 18 years of age will be included for FGDs. Healthcare providers will be excluded.

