#### Phase IV—Capacity building of healthcare providers

The capacity building of healthcare providers will be done by periodic short term training programs. A team of national experts for snakebite management (Expert group STG, 2017) will provide training to master trainers at each study site. Total six master trainers, including two from State Public Health Department, two Senior MOs from SDH/DH, and two MOs from PHC/RH/CHC, will be trained per block. The training will involve lectures and practical demonstrations to cover all aspects of snakebite management including signs and symptoms of SBE, how to suspect/recognize snakebite, management of sever cases, anti-venom use, laboratory examinations, referral and discharge criteria. Knowledge gaps identified in phase III will also be covered in the training sessions.

All master trainers will be provided quick reference guides and treatment flyers, prepared as per the STG, 2017. The master trainers along with site investigators will conduct training programs for all the MOs every six months for two years. The national expert team will provide technical support for these regional trainings. Trained MOs will further train around 600 ASHAs, Auxiliary Nurse Midwives (ANMs) and Multipurpose Workers (MPWs) at their respective health facilities on first aid skills, immobilization techniques and cardiopulmonary resuscitation. Quick reference charts as per STG (2017) and training manuals in regional languages will be given to healthcare providers and also displayed in examination rooms and indoor wards of health facilities. Site investigators will make periodic visits to health facilities for supportive supervision, post-training follow up and grievance redressal.

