#### Phase V—Impact evaluation of interventions

FGDs will be conducted in the study areas to evaluate the post-intervention community knowledge with the same methodology as discussed in Phase I, two months after the educational intervention. Pre- and post-training evaluations will be done to assess knowledge retention and the impact of training on the healthcare providers. Prospective data will be collected from the health facilities after the capacity building training of Medical Officers in study blocks for a period of one year. Incidence and case fatality rate in the study blocks will be calculated based on the prospective data. The impact of capacity building on the healthcare system will be assessed by comparing prospective data with the retrospective (pre-intervention) data.

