### Statistical analysis

The baseline data will be analyzed separately for different strata (Gender-wise, Age-wise, seasonal variation, distribution of venomous and non-venomous snakebite, site of snakebites, and categorization of snakebite based on the sign and symptoms of envenomation). The differences across strata will be investigated using appropriate statistical tests based on the nature of the variables. The Chi square and Fisher’s Test would be used to compare categorical variables while the independent t-test would be used to compare continuous variables. To check the factors associated with the incidence of snakebite, bivariate regression models will be used and results will be presented through odds ratios. The primary outcome will be reduction in the incidence of snakebite cases per 100000 population and a reduction in the case fatality rate in the study areas at the end of two years, measured by comparing the pre- and post-intervention data on the incidence of snakebite and mortality in the four study blocks. The secondary outcomes will include reduction in mean bite to needle time, reduction in the proportion of snakebite victims referred to higher facilities for management, increase in the proportion of MOs providing treatment as per STG 2017, mean increase in the number of vials of anti-venom administered to victims, reduction in the proportion of cases with severe complications including reduced kidney failure and amputation rate. Data from interviews of healthcare providers will be analyzed further for frequency. A summative index will be developed from the knowledge test of health workers. Two sample t-test will be used to compare the change in the knowledge of Medical Officers and the healthcare workers after the training. A p-value < 0.05 will be considered statistically significant. All the quantitative data will be entered and analyzed using the statistical package SPSS (version 26.0; IBM Corporation, Armonk, NY, USA).

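### Kidney failure is compared before and after training from routine hospital records, so a change in how often it is tested for and recorded can bias the crude proportion in either direction

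*Protocol article*

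**What the plan says.** All references are to the protocol article.

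- **Outcome (Statistical analysis).** One secondary outcome is a "reduction in the proportion of cases with severe complications including reduced kidney failure and amputation rate".
- **Source (Development of data collection tools and their validation).** For the retrospective and prospective forms alike, "Hospital records will be used for form filling".
- **Baseline (Phase I).** "Two-year retrospective data (01 January 2020 to 31 December 2021) will be collected from all the public health facilities in study areas". District hospitals and the medical colleges that receive severe cases are included.
- **Follow-up (Phase V).** The prospective records span twelve months and begin only once the Medical Officers have been trained.
- **Contrast (Phase V).** "The impact of capacity building on the healthcare system will be assessed by comparing prospective data with the retrospective (pre-intervention) data". All four blocks receive the training, so none serves as a concurrent control.
- **Training content (Phase IV).** It covers "signs and symptoms of SBE, how to suspect/recognize snakebite, management of sever cases" and also "anti-venom use, laboratory examinations, referral and discharge criteria". It is repeated every six months for two years and supported by wall charts and supervisory visits.

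**The concern.** Unless kidney failure is clinically obvious, it usually enters a routine record because someone ordered a test and wrote down the result. Here the intervention includes teaching on laboratory examinations, and the outcome is read from the records that the trained staff produce. The intervention may therefore change the measurement as well as the patients' outcomes. With no untrained block observed over the same year, a change in detection cannot be separated from a change in disease.

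The fourth study objective is the effect of the interventions on mortality and morbidity, and kidney failure is one of the two complications named for the morbidity part. A crude difference that mixes true change with detection could understate a benefit, hide it or overstate it. If the forms do not record in both periods whether a test was done, no later analysis can disentangle the two.

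**Working it through.** The article gives no kidney-failure rate, testing rate or effect size, so there is no figure to reproduce. Every rate below is an assumption chosen to show the range.

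**Formula.** Let RR be the true after/before ratio of kidney failure. Let s0 and s1 be the shares of true kidney-failure cases that reach the record before and after training. Let g be the growth in recorded snakebite cases from added mild bites without kidney failure. Then

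recorded ratio = RR × (s1/s0) / (1 + g).

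**When a true reduction is recorded as a rise (g = 0).** This needs s1/s0 > 1/RR:

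| True RR | Detection must rise by more than |
|---|---|
| 0.9 | 1.11 |
| 0.8 | 1.25 |
| 0.7 | 1.43 |
| 0.6 | 1.67 |
| 0.5 | 2.00 |

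Because s1 cannot exceed 1, reversal also requires s0 < RR. For a 30% reduction, fewer than 70% of cases must have been detected at baseline.

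**Illustrations (true baseline proportion 5%, g = 0).** The 5% cancels from the ratio.

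| Detection before → after | True RR | Recorded before | Recorded after | Ratio |
|---|---|---|---|---|
| 40% → 70% | 1.0 | 0.05 × 0.40 = 2.0% | 0.05 × 0.70 = 3.5% | 1.75 |
| 40% → 70% | 0.7 | 2.0% | 0.035 × 0.70 = 2.45% | 1.225 |
| 50% → 80% | 0.7 | 0.05 × 0.50 = 2.5% | 0.035 × 0.80 = 2.8% | 1.12 |
| 60% → 70% | 0.7 | 0.05 × 0.60 = 3.0% | 2.45% | 0.82 |

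The last row is dilution only: a 30% reduction reads as 18%.

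**The opposite bias (g > 0).** Take RR 0.7 and detection 50% → 80%:

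- g = 20%: 0.7 × 1.6 / 1.2 = 0.93
- g = 50%: 0.7 × 1.6 / 1.5 = 0.75

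With detection unchanged and g = 20%, 0.7 / 1.2 = 0.58, so the benefit is overstated.

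**Why the share tested helps (g = 0, RR 0.7, share tested 40% → 70%).**

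- If testing is unrelated to severity, the ratio among all cases is 1.225. Among those tested it is (2.45/70) / (2.0/40) = 3.5% / 5.0% = 0.70, the true value.
- If every true case is tested in both periods, the ratio among all cases is 3.5% / 5.0% = 0.70, the true value. Among those tested it is (3.5/70) / (5/40) = 5.0% / 12.5% = 0.40, which is too favourable.

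Neither proportion is right in both situations. Together they span the true ratio when selection for testing lies between these extremes.

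**The case against.** The strongest reply has five parts.

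1. **The change in detection is inferred.** No testing rate is given, and the recognition taught is of snakebite and its signs, not of kidney failure. The direct link is the laboratory item alone. This stands: the point is that detection may change, not that it does.
2. **Severe cases may already be tested at baseline.** District hospitals and medical colleges are covered, and the forms have a follow-up section for transferred patients. This stands as a damping factor, since with baseline detection at or above 70% a 30% reduction cannot be reversed. It is not complete protection: fewer onward referrals is itself a secondary outcome, which would change where cases are tested and recorded.
3. **The bias can run the other way.** Community awareness and recognition training may bring more mild bites into the records. This stands and is built into the formula. It makes the direction uncertain, but does not make the crude difference interpretable.
4. **Definitions and adjusted analyses may sit in the full protocol or analysis plan.** Agreed, and their absence is not counted here. What the article does describe does not reach this problem: tool validation and data verification concern the forms and data entry, and the extra sources named in the Discussion are there to capture deaths.
5. **This is one component of one secondary outcome.** True. The primary outcomes are incidence and case fatality.

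A reader might infer that the training will make recorded kidney failure rise, so that an effective programme is bound to look harmful. The documents do not support that: they give no detection rates, reversal needs a sizeable rise from a fairly low baseline, and the denominator may grow as well.

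**Conclusion.** The concern holds in a limited form. The stated design compares kidney failure from routine records across a training that covers laboratory examinations, without a concurrent control and with no described step to make ascertainment comparable. The crude before/after proportion is therefore open to bias of unknown size and direction. Under the assumed values with a true RR of 0.7, recorded ratios run from 0.58 (detection constant, 20% more recorded cases) to 1.225 (detection 40% → 70%, no extra cases).

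These figures assume that kidney failure is recorded only when detected, that there are no false positives, and that the added bites carry no kidney failure. Amputation is much less sensitive to testing. The article names it alongside kidney failure but does not say that the two form a single composite.

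It may also be tempting to conclude that kidney failure should give way to dialysis or mechanical ventilation as an endpoint. The documents do not support that either. Dialysis usually presupposes that kidney failure was found, both depend on access and referral, the Introduction reports that emergency ventilation is lacking at primary centres, and referral is among the things the programme aims to change.

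This is an inexpensive improvement to a secondary outcome. It does not affect the primary outcomes.

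**What to change.** In the Statistical analysis section and on the retrospective and prospective forms:

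- Abstract kidney failure with one definition in both periods.
- Add one yes/no field: kidney-function test on record.
- Report the share tested in each period beside the kidney-failure proportion, both among all cases and among those tested.
- Report amputation separately.
- State that no conclusion about morbidity will be drawn from the crude kidney-failure difference if the share tested differs between periods.
- Dialysis may be shown as a supporting measure, but should not replace the outcome.

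The cost is one extra item abstracted from records already being read, and a few sentences of text. The drawback is that the tested-only proportion depends on who is selected for testing, so it must be read with the all-cases proportion and not in its place. The fix also does not remove the effect of a growing denominator, which should be acknowledged when the results are interpreted.

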#### Phase III—Evaluation of the healthcare providers

Assessment of the basic knowledge, awareness, and perceptions on snakebite management and preventions among healthcare providers will be conducted. All the Medical Officers and Peripheral Health Workers from the study blocks who agree to participate will be included in the study. Each block will have approximately 40 MOs; so nearly 160 MOs will be assessed during the study. Similarly, around 600 peripheral workers (150 per block) will also be evaluated. Actual numbers may vary as the MOs or healthcare workers are frequently transferred in the health system.

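### The two-sample t-test named for the change in provider knowledge does not fit a pre/post evaluation of largely the same staff

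*Protocol article*

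**What the plan says.** All references are to the protocol article.

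- **Statistical analysis** names the test: "Two sample t-test will be used to compare the change in the knowledge of Medical Officers and the healthcare workers after the training". On the score it says: "A summative index will be developed from the knowledge test of health workers". For continuous variables in general, the section names the independent t-test. No paired test or repeated-measures model appears anywhere in the article.
- **Phase V** describes the comparison: "Pre- and post-training evaluations will be done to assess knowledge retention and the impact of training on the healthcare providers".
- **Development of data collection tools and their validation** gives the instruments: "Separate questionnaires for peripheral workers and Medical Officers (MO) at facilities would be developed based on the STG, 2017".
- **Phase III** gives the numbers. For Medical Officers (MOs): "Each block will have approximately 40 MOs; so nearly 160 MOs will be assessed during the study". About 600 peripheral workers, 150 per block, are also to be evaluated. It adds: "Actual numbers may vary as the MOs or healthcare workers are frequently transferred in the health system".
- **Phase IV** has all MOs trained. The trained MOs then train the roughly 600 workers at their own facilities.

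**The concern.** The sentence on the t-test can be read in two ways, and neither matches the aim in Phase V.

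**Pre versus post within a cadre.** Retention is a within-person quantity, and the staff assessed in Phase III are the pool trained in Phase IV. Many people will contribute two correlated scores. A two-sample test treats the two sets as coming from different people, so its standard error is wrong. It also compares unlinked means, so a change in who sits the test can look like a change in what staff know.

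**MOs versus workers.** The two groups are independent here, but their scores come from different questionnaires. The result would say which cadre's index moved more, not whether training raised knowledge in either.

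At stake is the article's direct measure of whether the training worked: the precision of the estimate, and whether it measures learning at all. Linkage also has to be set up in time. If pre-test forms carry no identifier, pairing cannot be recovered later.

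**Working it through.** **Nothing to reproduce.** The article gives no effect size, SD, power or sample-size calculation for knowledge. The head counts agree: 4 × 40 = 160 MOs and 4 × 150 = 600 workers.

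**Inputs from the article.** n = 160 and n = 600; significance level 0.05.

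**Assumed, because the article does not give them.** Two-sided testing; equal SD before and after; pre/post correlation rho of 0.3, 0.5 or 0.7; fraction f of staff tested at both times; true shift of 0.2 SD (MOs) or 0.1 SD (workers). A normal approximation is used, and clustering by facility is left out at this stage.

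**Step 1. Standard errors with full overlap (f = 1).**
- Two-sample: SD × sqrt(2/n)
- Paired: SD × sqrt(2(1 − rho)/n)
- Ratio: 1/sqrt(1 − rho), whatever the n

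**Step 2. True error rate of the two-sample test.** It is 2 × [1 − Phi(1.96/sqrt(1 − rho))]. At rho = 0.5, 1.96/0.707 = 2.77, which gives 0.0056.

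**Step 3. Power for a true shift d (in SD units).**
- Two-sample: Phi[(d − 1.96 × sqrt(2/n)) / sqrt(2(1 − rho)/n)]
- Paired: Phi[d / sqrt(2(1 − rho)/n) − 1.96]

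For MOs at rho = 0.5, sqrt(2/160) = 0.1118 and sqrt(1/160) = 0.0791. Two-sample: Phi[(0.2 − 0.2191)/0.0791] = 0.40. Paired: Phi[2.53 − 1.96] = 0.72.

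| rho | SE overstated by | True alpha | MOs, 0.2 SD: two-sample / paired power | Workers, 0.1 SD: two-sample / paired power |
|---|---|---|---|---|
| 0 | 1.00 | 0.05 | 0.43 / 0.43 | 0.41 / 0.41 |
| 0.3 | 1.20 | 0.019 | 0.42 / 0.57 | 0.39 / 0.54 |
| 0.5 | 1.41 | 0.0056 | 0.40 / 0.72 | 0.37 / 0.69 |
| 0.7 | 1.83 | 0.0003 | 0.38 / 0.90 | 0.34 / 0.88 |

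At rho = 0.5, the shift detectable with 80% power is 0.286 SD (two-sample) against 0.221 SD (paired) for MOs, and 0.148 against 0.114 SD for workers.

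**Step 4. Partial overlap.** If only a fraction f is tested at both times, f × rho replaces rho in Steps 1 and 2. At rho = 0.5:

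| f | f × rho | SE overstated by 1/sqrt(1 − f × rho) | True alpha |
|---|---|---|---|
| 0.5 | 0.25 | 1.15 | 0.024 |
| 0.7 | 0.35 | 1.24 | 0.015 |
| 0.9 | 0.45 | 1.35 | 0.008 |

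The error shrinks as overlap falls but does not vanish.

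**Step 5. Transfers.** With equal numbers at both times, the difference in unlinked means is f × (mean change in those who stayed) + (1 − f) × (post-test mean of joiners − pre-test mean of leavers). The second term is not learning. It is zero only if f = 1 or if those two means happen to agree.

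**Step 6. The other reading.** No arithmetic applies. The questionnaires differ by cadre, and the article states no common scale for the index. A difference between the two mean changes therefore has no defined unit, and neither mean change is itself tested against zero.

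**The case against.** **The wording may be loose.** The section names the independent t-test separately, so the different term here may stand for a comparison of two sets of scores from the same people. That is possible, but nothing in the article says so, and clearing it up takes the same one-sentence change.

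**Overlap is not stated.** A reader might infer that the same 160 MOs and 600 workers are all tested twice. The article does not say this: the numbers are approximate, participation is by agreement, and transfers are expected. This stands. The full-overlap figures are an upper end, and Step 4 shows how far they fall.

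**Direction of the error.** A reader might infer that the wrong test could produce a false claim that training worked. Ignoring positive correlation does the opposite: p-values are too large and intervals too wide. With full overlap the estimated mean change is the same under either test. This stands as far as pairing goes. It does not make the test safe in every respect. Workers are trained by MOs at their own facilities, so their gains may cluster by facility. Ignoring that makes the standard error too small, by an amount the article gives no figures to estimate.

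**The MO-versus-worker reading.** A reader might call this reading invalid. A two-sample test of change between two distinct cadres is legitimate, and the index is still to be developed, so its scaling is open. What remains is that it answers a different question from the one in Phase V.

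**Weight.** Knowledge change is not among the primary or secondary outcomes in the Statistical analysis section, and the stated objectives do not name a pre/post knowledge test. This stands and limits the severity.

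**Conclusion.** The named test does not match the evaluation that Phase V describes. This is a stated choice, not a detail left to an analysis plan. On the pre/post reading, the cost of ignoring pairing is lost power and over-wide intervals: a standard error 1.20 to 1.83 times too large for rho from 0.3 to 0.7 with full overlap, and less with partial overlap. Unlinked means add a possible bias from transfers, whose size and sign cannot be worked out from the article. On the cadre reading, the effect of training is not tested.

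The correlations, overlap and effect sizes are assumptions; at rho = 0 the two tests coincide. Severity is moderate. The documents do not support a claim that the trial's main conclusions are affected.

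**What to change.** Issue a study ID at the pre-test and carry it on every later knowledge form. Replace the sentence on the t-test with:

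> Within MOs and within peripheral workers separately, the pre-to-post change in the summative index will be tested with a paired t-test on linked scores; a mixed model with a participant random effect will be used to keep staff with only one score, and for peripheral workers standard errors will allow for clustering of the change by facility.

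Two points on the wording:

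- A facility random intercept would not be enough. It largely cancels from a within-person difference, so the allowance has to be for variation between facilities in the change itself.
- The paired result should be shown beside the mixed model, because staff with one score bring some between-person comparison back in.

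If a comparison between cadres is also wanted, it should rest on common items or a standardised score.

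The cost is one sentence, an ID field and the small effort of linking scores. The ID has to be in place before the pre-test.
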